## Baseline results

In May 2014, the first participant was included into the study. Because of slow recruitment, in January 2018 it was decided to stop further inclusion of participants and complete the protocolled follow-up duration with the included cohort (*N* = 84). At this point, it had become clear that it was not realistic to assume that enough participants would be included to reach the originally defined composite primary endpoint (Tab. 3). Instead of a composite dichotomous endpoint, i.e. using the pre-specified cut-off values, individual components of the primary endpoint will now be analysed on a continuous scale to investigate possible significant differences. The statistical analysis plan was amended accordingly, and the decision to amend the study design, i.e. to stop inclusion of participants and to continue with the included cohort, was supported by the DSMB and the medical ethics committee. The primary objective remains showing that eplerenone retards disease progression. The majority of participants have now finished the study and the remaining participants are expected to finish in 2021.

An overview of the baseline characteristics of the 84 participants is provided in Tab. 4. By design, at baseline, all participants were in NHYA class I and had an LVEF > 45% and less than 2500 ventricular premature complexes (VPCs) during 24-hour Holter monitoring. Mean LVEF was 60% (±0.04). The median number of VPCs was 8 (0-1861). Baseline CMR scans were obtained for all 84 participants, but image quality was insufficient to perform adequate analyses in six cases. In the remaining 78 cases, as many as 14 cases (18%) showed LGE, mainly in the inferolateral left ventricular wall, suggestive of myocardial fibrosis. The six cases with insufficient image quality will be included for analysis of the other endpoints. An illustrative example is shown in Fig. 2. There were no statistically significant differences between the two groups in any of the baseline characteristics.

**Table 4 Tab4:** Baseline characteristics: no statistical differences between eplerenone and control group

	All	Eplerenone group	Control group
Number, *n*	84	42	42
Age at inclusion, years (SD)	39.5 (±13.1)	40.2 (±13.0)	38.8 (±13.4)
Male sex, *n* (%)	37 (44)	18 (43)	19 (45)
Body mass index, kg/m^2^ (SD)	25.7 (±4.8)	26.5 (±5.6)	24.9 (±3.6)
Systolic blood pressure, mm Hg (SD)	124 (±16)	128 (±17)	121 (±13)
Diastolic blood pressure, mm Hg (SD)	74 (±11)	75 (±10)	74 (±11)
ECG repolarisation abnormalities, *n* (%)	18 (21)	13 (31)	5 (12)
VPC, *n* (range)	8 (0–1861)	8 (0–1498)	12 (0–1861)
LVEDV, ml (SD)	157 (±28)	160 (±23)	154 (±34)
LVEF, % (SD)	60 (±0.04)	60 (±0.04)	59 (±0.05)
LV-LGE, *n* (%)	14 (18)	9 (22)	5 (13)
RVEDV, ml (SD)	178 (±34)	179 (±27)	176 (±42)
RVEF, % (SD)	52 (±0.04)	52 (±0.04)	51 (±0.04)

*SD* standard deviation*, ECG* electrocardiogram, *VPC* ventricular premature complexes, *LVEDV* left ventricular end-diastolic volume, *LVEF* left ventricular ejection fraction, *LV-LGE* left ventricular late gadolinium enhancement, *RVEDV* right ventricular end-diastolic volume, *RVEF* right ventricular ejection fraction

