### Study organisation and monitoring

This is an investigator-initiated study organised by the executive steering committee, which is based in the Department of Cardiology, University Medical Center Groningen, Groningen, the Netherlands. The executive steering committee is responsible for overall supervision of the study, policy decisions, protocol amendments, publications and presentations. An independent DSMB monitors the overall conduct of this study by receiving and reviewing reports of serious adverse events, reviewing periodic reports of safety data and establishing ‘stopping rules’ for the trial for safety reasons only.

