The primary objective of this study is to assess the effect of eplerenone on disease onset and progression. To comply with daily clinical practice and demonstrate overall disease progression, a composite endpoint of CMR parameters (CMR volumes, systolic function and fibrosis), electrocardiographic parameters (QRS voltage, ventricular ectopy), signs and/or symptoms related to DCM and ACM, and cardiovascular death is adopted as the primary endpoint. Serum markers of fibrosis, apoptosis, haemodynamic status and inflammation are measured to investigate whether they can predict disease progression. Of note, as discussed in the baseline results, the actual number of participants was lower than projected. As a result, we will now perform an adapted assessment of the primary endpoint but are hopeful that meaningful results will be obtained. As to their clinical characteristics, the participants are a good reflection of clinical practice; indeed, many of these presymptomatic PLN p.Arg14del carriers already have subtle signs of disease, including repolarisation abnormalities of the ECG and frequent VPCs. Moreover, LGE on CMR, indicative of fibrosis, was observed in as many as 18% of the participants at the start of the study thereby supporting the rationale to study the effect of eplerenone.

In conclusion, iPHORECAST is a multicentre, randomised, controlled trial, designed to examine whether treatment with eplerenone in presymptomatic PLN p.Arg14del carriers can prevent or delay disease onset.

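### The pre-specified dichotomous composite is replaced, not supplemented, late in an open-label trial, so no primary analysis fixed as primary before outcome data accrued remains; other sections still call the composite primary

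*Protocol article*

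**What the plan says.** Everything comes from the protocol article.

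- **Timing.** Baseline results: "In May 2014, the first participant was included into the study", and "in January 2018 it was decided to stop further inclusion of participants and complete the protocolled follow-up duration with the included cohort". The reason given is slow recruitment, with 84 carriers enrolled.
- **Endpoint change.** The same paragraph continues: "At this point, it had become clear that it was not realistic to assume that enough participants would be included" to reach the composite. Then comes the replacement: "Instead of a composite dichotomous endpoint, i.e. using the pre-specified cut-off values, individual components of the primary endpoint will now be analysed". The aim of the new analysis is worded as "individual components of the primary endpoint will now be analysed on a continuous scale to investigate possible significant differences". No single component is named as the new primary endpoint.
- **Analysis plan.** "The statistical analysis plan was amended accordingly", with no date.
- **Composite still primary elsewhere.** The Abstract (Methods) and the Study endpoints section with Table 3 define the primary endpoint as the multiparametric assessment, in Table 3 with cut-offs. Statistical analysis assigns the primary outcome Kaplan-Meier curves and a stratified log-rank test. The Discussion repeats the list, ending "signs and/or symptoms related to DCM and ACM, and cardiovascular death is adopted as the primary endpoint", and a few sentences later announces an adapted assessment.
- **Who amends.** Study organisation and monitoring: "The executive steering committee is responsible for overall supervision of the study, policy decisions, protocol amendments, publications and presentations". The committee is based at the coordinating centre.

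**The concern.** In an open-label trial, a primary analysis fixed before outcomes accrue protects against choosing the endpoint in the light of results. Blinded CMR reading and blinded adjudication protect how each outcome is measured. They do not protect the choice of which outcome becomes primary, or on which scale.

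Here the one analysis that was fixed as primary in advance is worded as replaced, when some carriers were already due at the end of follow-up. Yearly ECG, Holter and exercise tests feed components of the composite directly. Reaching any component triggers a CMR and a recorded end date, so composite events were recognised as they occurred. If the continuous components later show a difference and the composite is not reported, a reader cannot check that result against the analysis planned at the outset. Because the sections disagree, the reader also cannot tell whether the composite will be reported at all.

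**Working it through.** **1. The plan's own sample size.** Inputs from Sample size estimation: 50% events on control, 25% on eplerenone (a 50% relative reduction), 80% power, alpha 0.05. Sidedness is not stated; two-sided is assumed. Exact power of Fisher's test by binomial enumeration is 79.4% at 63 per group and 80.2% at 64. The stated 64 per group (128 in total) is reproduced. Allowing for loss: 128/0.90 = 142.2, so 143; 128/0.85 = 150.6, so 151. The target of 150 fits.

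**2. Timing.** May 2014 to January 2018 = 4 × 12 − 4 = 44 months. Follow-up is 36 months, so carriers included by about January 2015 (the first 44 − 36 = 8 months) were due at 36 months. The article does not say how many there were. Under even recruitment (an assumption), 84 × 8/44 = 15.3, or about 15 carriers. Front-loaded recruitment would give more and back-loaded recruitment fewer.

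**3. Power of the composite with the 84 enrolled.** Same rates, 42 per arm, before dropout.

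| Method | Calculation | Power |
|---|---|---|
| Fisher exact | binomial enumeration, n = 42 per arm | 60% |
| Pooled z | SE under the null = √(2 × 0.375 × 0.625/42) = 0.1056; SE under the alternative = √((0.25 + 0.1875)/42) = 0.1021; (0.25 − 1.96 × 0.1056)/0.1021 = 0.42 | 66% |
| Log-rank (Schoenfeld) | HR = ln 0.75/ln 0.50 = 0.415; events = 42 × (0.50 + 0.25) = 31.5; √31.5/2 × 0.879 − 1.96 = 0.51 | 69% |

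After 10–15% loss (38 or 36 per arm) the pooled z gives 62% or 59%.

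**4. Precision the composite would still have.** With 31.5 events, the approximate SE of the log hazard ratio is 2/√31.5 = 0.356. At the planned effect the 95% CI is exp(−0.879 ± 1.96 × 0.356), about 0.21 to 0.83 around 0.415, before dropout. That is wide, but still informative about direction and size.

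**5. The sections side by side.** Baseline results replaces the composite. The Abstract, Study endpoints and Statistical analysis present it as primary without qualification. The Discussion says it is adopted and then that its assessment is adapted. These cannot all describe the current plan.

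**The case against.** The strongest reply is that the change is openly disclosed with a plausible reason, and that what it promotes is not new. Table 3 already lists every individual component as a secondary endpoint, together with DCM and ARVC diagnosis, sustained ventricular arrhythmia and cardiovascular hospitalisation. Statistical analysis already foresees repeated-measurement analysis of changes over time. This stands. A reader might infer that no analysis at all predates the outcome data; the documents do not support that. What is new is primary status and the continuous scale in place of cut-offs.

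Second, few of the relevant data may have existed. Five of the eight components in Table 3 are CMR measures, scheduled only at baseline and 36 months, so apart from event-triggered scans few CMR changes were available in January 2018. The core lab is blinded to allocation and the adjudication committee is independent and blinded. This also stands. A reader might infer that results by arm drove the change; nothing in the article shows it. For the same reason no inflated error rate can be attached to the switch, because the article does not say what was seen.

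Third, a reader might infer that the DSMB supported the new endpoint. Its support is spelled out as covering the stop of inclusion and continuation with the enrolled cohort, and Study organisation and monitoring limits its stopping rules to safety. It can be cited neither as endorsing the endpoint change nor as having seen efficacy by arm when the change was made.

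Fourth, an article may leave the amendment's date and its authors' access to data to the analysis plan, which is not shown. That weakens any complaint about silence. It does not answer the printed replacement of the composite, or the sections that contradict it.

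**Conclusion.** The point holds in limited form. At or after January 2018, about 44 months into an open-label trial, the composite is worded as replaced by its components on a continuous scale. No primary analysis then remains that was fixed as primary before outcome data accrued. January 2018 is explicitly the date of the inclusion stop; the endpoint change is linked to it only by context, and a later date would mean that more data had accrued.

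Slow recruitment justifies a more sensitive scale. It reduces the composite's power from 80% to about 60–69% before dropout (59–62% by pooled z after 10–15% loss), but does not make the composite uninformative. These figures assume the planned 50% and 25% rates and a two-sided 0.05 level; the log-rank figure also assumes proportional hazards. They take no account of the six carriers whose CMR components cannot be scored.

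**What to change.** 1. In Baseline results, change *Instead of* to *In addition to*. Analyse and report the Table 3 composite with its original cut-offs beside the continuous components, by the Kaplan-Meier and stratified log-rank analysis already given in Statistical analysis, with an effect estimate and 95% CI. A newly chosen test would defeat the purpose.
2. State how the six carriers without analysable baseline CMR enter the composite. Change in the five CMR components cannot be computed for them, so they could reach it only through the other three.
3. Reconcile the Abstract, Study endpoints, Statistical analysis, Baseline results and Discussion on what is primary and what is reported. Use one component list: the Abstract and Discussion include cardiovascular death, which Table 3 does not.
4. Date the amendment to the analysis plan and state whether its authors had seen outcome data by arm.

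The cost is wording and one further analysis of data collected by design. The downside is an additional, less precise result that may temper the conclusion.

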### Study endpoints

The primary and secondary endpoints are listed in Tab. 3. The primary endpoint is a multiparametric assessment of disease progression defined as a responder-based composite primary endpoint (Tab. 3). If one of the predefined parameters of the composite primary endpoint is reached, CMR imaging is performed and study end date recorded. After a follow-up period of 3 years, outcomes will be assessed by an independent adjudication committee blinded to the allocated group. In case of a favourable trend (but no significant effect as yet), the DSMB may advise continuing the study for 2 more years (“adaptive design”).

**Table 3 Tab3:** Primary and secondary endpoints

*Primary endpoint*^a^
LV end-diastolic volume, increase > 10% (assessed with CMR)
LV ejection fraction, absolute decrease > 5% (assessed with CMR)
RV end-diastolic volume, increase > 10% (assessed with CMR)
RV ejection fraction, absolute decrease > 5% (assessed with CMR)
Late enhancement, absolute increase > 5% (assessed with CMR)
QRS voltage, decrease > 25% (ECG, measured in I, II and III in mV)
Occurrence of non-sustained ventricular tachycardia (Holter monitoring, exercise testing)
Heart failure signs and/or symptoms or arrhythmias necessitating medical treatment according to the guidelines and likely due to arrhythmogenic cardiomyopathy
*Secondary endpoints*
All individual components of the primary endpoint
Diagnosis of DCM (according to Mestroni criteria [19])
Diagnosis of ARVC (according to revised task force criteria [18])
Development of global or regional dysfunction and structural alterations (according to revised task force criterion 1 [18])
QRS axis (12-lead ECG)
Conduction intervals (PR interval, QRS duration [12-lead ECG; SA-ECG])
STT segment changes (12-lead ECG)
Change in biomarkers
Occurrence of sustained ventricular tachycardia or ventricular fibrillation
Hospitalisation for a cardiovascular reason

*LV* left ventricular, *CMR* cardiac magnetic resonance*, RV* right ventricular,* ECG* electrocardiogram,* DCM* dilated cardiomyopathy, *ARVC* arrhythmogenic right ventricular cardiomyopathy,* SA-ECG* signal-averaged electrocardiography

^a^The primary endpoint is a multiparametric assessment of disease progression defined as a responder-based composite primary endpoint. If one of the predefined parameters of the composite primary endpoint is reached, CMR imaging is performed and study end date recorded

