### Sample size estimation

This clinical trial was designed based on the assumptions that 50% of the presymptomatic PLN p.Arg14del carrier group without treatment will reach the primary endpoint within 3 years and that treatment with eplerenone is expected to reduce this percentage by 50%. To ensure at least 80% power to detect a difference between the control group and the eplerenone group, at a significance level of 0.05, 128 carriers (64 in each group) are needed. To account for 10–15% loss to follow-up during the study, we aimed to include 150 subjects.

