### Statistical analysis

After completion of the study, all eligible carriers who have been randomised to the treatment arm and received at least 1 dose of eplerenone will be used in the analyses of the primary and secondary efficacy endpoints, as well as in the safety analysis. Safety will be assessed by summarising the incidence and type of adverse events and the changes in laboratory parameters. The proportion of carriers experiencing serious adverse events and the proportion of carriers with noteworthy changes in laboratory parameters will be compared between treatment groups. The analysis of primary endpoints and secondary endpoints will be performed according to their assigned treatment group in accordance with the intention-to-treat principle. Additional analysis sets may be used in exploratory analyses. The number of subjects withdrawing from the study will be tabulated by their reasons for withdrawal and by treatment group. Potenzial biases due to withdrawal of subjects will be investigated. Baseline characteristics will be compared using chi-squared test (or Fisher’s exact test if appropriate). If differences are found, caution will be exercised when interpreting the results of the analyses between groups and methods may be modified to adjust for this difference.

The primary outcome will be presented by Kaplan-Meier curves for the treatment group, followed by the stratified log-rank test using stratification variables. Multivariate analysis will also be used to compare the endpoints between the two groups, adjusting for other variables including sex, age and screening centre. For missing data, the last observations made will be used. Unless stated otherwise, all secondary analyses will be performed using the same subjects included in the primary analysis. Secondary variables will be analysed using an appropriate statistical test, depending on the nature of the variable. Changes in parameters over time in the different treatment groups will be analysed using repeated measurement analysis or techniques that evaluate the timing of endpoints, when appropriate. For all tests, a *p*-value < 0.05 is considered statistically significant. Statistical analysis will be performed in SPSS (IBM SPSS Inc., Chicago, IL, USA; newest version at moment of analysis).

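### After the 2018 amendment the primary objective rests on several component tests, each at p < 0.05, and the article shows no rule for which of them decides

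*Protocol article*

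**What the plan says.** The original design had a single primary comparison. Table 3 lists eight parameters, and reaching any one of them made a participant a progressor. The Sample size estimation section sizes the trial for that comparison: "at a significance level of 0.05, 128 carriers (64 in each group) are needed", for 50% against 25% progressing within 3 years at 80% power. The Statistical analysis section gives the matching test: "The primary outcome will be presented by Kaplan-Meier curves for the treatment group, followed by the stratified log-rank test using stratification variables".

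The Baseline results section reports that inclusion was stopped in January 2018 with 84 participants (42 per group), and that the dichotomous composite gives way to its parts: "individual components of the primary endpoint will now be analysed on a continuous scale to investigate possible significant differences". It adds that the statistical analysis plan was amended to match and that the primary objective is unchanged, namely to show that eplerenone slows progression.

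The only threshold in the article is general: "For all tests, a *p*-value < 0.05 is considered statistically significant".

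**The concern.** One test at 0.05 limits the chance of a false claim to 5%. Several tests at 0.05, any of which could support the same claim, do not. The components were already secondary endpoints in Table 3. What changed is that they now carry the primary objective while the threshold stayed the same.

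Two further points leave the deciding analysis unclear:

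- Six of the eight components are measurements: LV and RV end-diastolic volume, LV and RV ejection fraction, late enhancement and QRS voltage. The other two are yes/no: non-sustained ventricular tachycardia, and heart failure or arrhythmias needing treatment. These have no continuous scale, and the amendment does not say how they enter.
- The Statistical analysis section still attaches Kaplan-Meier curves and a log-rank test to the primary outcome, which fits the former composite and not continuous components.

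At stake is whether one nominally significant parameter out of six or eight could be reported as meeting the primary objective, in a population for which the Introduction says no evidence-based treatment exists.

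**Working it through.** **Inputs from the article.** Alpha 0.05 for every test (Statistical analysis); 50% against 25% at 3 years, 80% power, 64 per group (Sample size estimation); 42 per group enrolled (Table 4); eight components, six of them measurements (Table 3).

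**Assumptions.** Tests are two-sided; the article does not say, but this reproduces its sample size. The correlation between component test statistics is not given, so I use 0 to 0.9, equal for all pairs. Any one significant component counts as success.

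**1. The plan's own figure.** Exact power of a two-sided Fisher test for 50% against 25%: 79.4% at 63 per group and 80.2% at 64. The stated 64 per group is reproduced.

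**2. Familywise error, independent tests.** The chance of at least one p < 0.05 under no effect is 1 − 0.95^k.

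- k = 6: 1 − 0.95^6 = 26.5%
- k = 8: 1 − 0.95^8 = 33.7%

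For false results favouring eplerenone only, it is 1 − 0.975^k: 14.1% for k = 6 and 18.3% for k = 8, against 2.5% for one test.

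**3. Familywise error, correlated tests.** Simulation, 400,000 draws of equicorrelated normal statistics (the column for 0 is from the formula):

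| Correlation | 0 | 0.3 | 0.5 | 0.7 | 0.9 |
|---|---|---|---|---|---|
| 6 tests, any p < 0.05 | 26.5% | 24.1% | 20.7% | 16.4% | 10.8% |
| 8 tests, any p < 0.05 | 33.7% | 30.0% | 25.1% | 19.1% | 11.9% |
| 6 tests, favouring eplerenone | 14.1% | 12.2% | 10.3% | 8.2% | 5.4% |
| 8 tests, favouring eplerenone | 18.3% | 15.2% | 12.5% | 9.5% | 6.0% |

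For correlations up to 0.7 the two-sided rate is 3.3 times (16.4/5) to 6.7 times (33.7/5) the nominal 5%. At 0.9 it is 2.2 to 2.4 times.

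**4. Precision at 42 per group.** Standardised difference detectable with 80% power, two-sample t-test:

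- at 0.05: 0.62 SD
- at 0.05/6 = 0.0083: 0.78 SD
- at 0.05/8 = 0.00625: 0.80 SD

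For the original composite (50% against 25%), Fisher's exact test has about 60% power at 42 per group. None of these figures allows for dropout.

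**5. Joint test against single-component tests.** Six components, correlation 0.3, 42 per group, by simulation:

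| True effect | Global (averaged) test | Any component significant after Bonferroni |
|---|---|---|
| 0.35 SD on all six | 70% | 51% |
| 0.7 SD on one, none on the rest | 13% | 73% |

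**The case against.** **The amended analysis plan may contain the rule.** This is the strongest objection. The article says that plan was changed, it is not shown, and an article often leaves a multiplicity rule to it. It stands as a limit: the finding is that no such rule is visible, not that none exists. It does not remove the point, because the article is not merely silent. It states 0.05 for all tests and keeps a confirmatory objective.

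**Independence is implausible.** Volumes and ejection fractions come from the same scan, so the 34% for eight independent tests is an upper end. This is fair, and it is why the range runs to 0.9. The inflation shrinks there to a little over twofold, but does not vanish.

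**Stronger readings that the article does not support.**

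- A reader might infer that the yes/no clinical components have been dropped. Nothing says so. All components remain secondary endpoints, and the Statistical analysis section fits the test to the type of variable. What is unclear is their place in the amended primary analysis.
- A reader might infer that the supersession is hidden or denied. It is not. The Baseline results section reports the change and the shortfall, and the Discussion, although it describes the composite as primary, also announces an adapted assessment. The remaining Kaplan-Meier and log-rank text describes the original design and needs alignment.
- A reader might infer that outcome data prompted the change, since the trial is open-label and the first participant entered in May 2014. The stated reason is slow recruitment, CMR reading and endpoint adjudication are blinded, and the DSMB and the ethics committee supported stopping inclusion. Nothing suggests that results were inspected.

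**Conclusion.** The point holds on what the article states. Separate component tests at 0.05 each, serving one retained confirmatory claim, do not keep the error rate at 5%. The familywise error is about 16–27% for six components and 19–34% for eight (correlation 0.7 down to 0), and 11–12% at 0.9. False results favouring eplerenone arise in about 8–18% (correlation 0.7 down to 0), against 2.5%.

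This rests on three conditions: the assumed correlations, reading any one significant component as success, and no overriding rule in the unseen amended plan. If that plan already names the deciding analysis and controls its error, what remains is to make the article agree with it.

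**What to change.** Unless the amended analysis plan already does so, settle the following before outcomes are compared by treatment group:

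1. **Name the analysis that decides the primary objective and hold it at two-sided 0.05.** Holm across the components, one named lead component, or a pre-specified global test would each do. Otherwise label the component results exploratory and withdraw the statement that the trial will show slower progression.
2. **Say how the two yes/no components enter**, since they cannot be analysed on a continuous scale.
3. **Align the Kaplan-Meier and log-rank text with the amendment**, and keep the original composite as a supporting analysis.
4. **State the precision for 42 per group**: 0.62 SD at 0.05, 0.78 SD at 0.05/6, 0.80 SD at 0.05/8, and about 60% power for the original composite.

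The edits are to wording, but there is a statistical price. Single-component claims need a stricter p-value. A global test gains power only if effects are similar across components and loses heavily if the effect sits in one (13% against 73% in the example above). Most participants had finished when the article was written, so the change should be dated and its reason given, to avoid the appearance of a post hoc choice.

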### Study population

Specific inclusion and exclusion criteria are listed in Tab. 1. Previously, all known PLN p.Arg14del carriers in the Netherlands, including all presymptomatic carriers, were registered in the PHORECAST registry (PHOspholamban RElated CArdiomyopathy Study; http://www.phorecast.nl). Recently, all carriers have been incorporated in the national arrhythmogenic cardiomyopathy (ACM) registry (www.acmregistry.nl) [17]. We used the PHORECAST registry to recruit eligible presymptomatic subjects. Study participants are between 18 and 65 years of age, have a New York Heart Association (NYHA) functional class of 1 and an LVEF greater than 45% (as measured by cardiac magnetic resonance [CMR]). For ARVC and DCM criteria, we used the revised task force and Mestroni criteria respectively [18, 19]. Carriers taking other cardiovascular medication, including diuretics, angiotensin-converting enzyme (ACE) inhibitors, angiotensin receptor blockers, mineralocorticoid receptor antagonists, beta-blockers and anti-arrhythmic medication, were excluded.

**Table 1 Tab1:** Key inclusion and exclusion criteria

*Key inclusion criteria*
PLN p.Arg14del carriers
Age ≥ 18 and ≤ 65 years
New York Heart Association functional class ≤ 1
LV ejection fraction ≥ 45 (measured with MRI)
*Key exclusion criteria*
Palpitations necessitating treatment (at the discretion of the attending physician)
A diagnosis of DCM (according to the Mestroni criteria [19]). Note: regional LV wall motion abnormalities are acceptable
A diagnosis of ARVC (according to the task force criteria [18])
Global or regional RV dysfunction and/or structural alterations (according to task force criterion 1 [18])
Ventricular premature complexes > 2500 during 24-hour Holter monitoring
Non-sustained ventricular tachycardia during Holter monitoring or exercise testing
History of sustained ventricular tachycardia or ventricular fibrillation
Hypertension requiring the use of antihypertensive drugs, or when this is anticipated within the coming 3 years
Evidence of ischaemic heart disease
Treatment with cardioactive medication
Hyperkalaemia (serum potassium > 5.0 mmol/l)
Severe renal dysfunction (eGFR < 30 ml/min/1.73 m^2^)
Severe hepatic impairment (Child-Pugh class C)
Women who are currently pregnant or report a recent pregnancy (last 60 days) or plan on becoming pregnant
Concomitant use of CYP3A4 inhibitors
Concomitant use of NSAIDs
Concomitant use of potassium-sparing agents

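### Carriers with an inadequate baseline CMR appear to be left out of the CMR comparisons, at odds with intention to treat and at an avoidable cost in precision

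*Protocol article*

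**What the plan says.** The Baseline results section of the protocol article states that "Baseline CMR scans were obtained for all 84 participants, but image quality was insufficient to perform adequate analyses in six cases". It bases the late gadolinium enhancement (LGE) count on the other 78 scans and then says: "The six cases with insufficient image quality will be included for analysis of the other endpoints". Table 4 heads its columns 84, 42 and 42 and gives no smaller denominator for the CMR rows.

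The same section reports that recruitment stopped at 84, and that the components of the primary endpoint will be analysed singly as continuous measures instead of as a dichotomous composite. Table 3 lists eight components. Five are CMR measures: LV and RV end-diastolic volume, LV and RV ejection fraction, and late enhancement.

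The Statistical analysis section says that primary and secondary endpoints will be analysed by assigned group under intention to treat, and that missing data will be replaced by the last observation made. It also allows repeated-measurement analysis where appropriate. Table 2 schedules CMR at the start and at 3 years only. The Study endpoints section adds that CMR is done when a component of the endpoint is reached.

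The Study population section ties LVEF at entry to CMR ("an LVEF greater than 45% (as measured by cardiac magnetic resonance [CMR"; Table 1: "LV ejection fraction ≥ 45 (measured with MRI"). The Baseline results section then describes the whole cohort as meeting the entry limits: "By design, at baseline, all participants were in NHYA class I", with LVEF above 45%.

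**The concern.** The article gives a rule for the six, and that rule does not fit its own analysis principle. If the six contribute only to the other endpoints, the CMR comparisons are made in a subset of the randomised carriers. The stated missing-data rule does not close the gap: carrying an observation forward needs an earlier observation, and a missing baseline has none. With CMR scheduled only twice, an analysis of change from baseline has nothing to work with for these carriers, even if their end-of-study scan is perfectly readable.

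The CMR measures are the majority of the components that now carry the primary objective. The cohort is 84 against a target of 150, so outcome data that can be used should not be given up without need.

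**Working it through.** **Inputs.** From the article: 84 randomised, 42 per arm; six inadequate baseline scans; LGE in 14 (18%) overall, 9 (22%) on eplerenone and 5 (13%) in control. Assumed: baseline–follow-up correlation r = 0.6 to 0.8; all six have a readable end-of-study scan; two-sided 5% level and 80% power for detectable differences; all other carriers complete.

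**1. The article's own figure.** 84 − 6 = 78. 14/78 = 17.9%, which rounds to the printed 18%; 14/84 = 16.7% does not. The LGE row therefore uses 78, although the column heading says 84.

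**2. Share affected.** 6/84 = 7.1% of randomised carriers, in up to five of eight components.

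**3. Which arms?** With 42 per arm, 9/42 = 21.4% and 5/42 = 11.9%, which do not match the printed 22% and 13%. The closest splits of 78 are:

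| Eplerenone / control | LGE % | Implied missing |
|---|---|---|
| 40 / 38 | 22.5 / 13.2 | 2 vs 4 |
| 41 / 37 | 22.0 / 13.5 | 1 vs 5 |

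No split rounds conventionally to both printed figures, so the split by arm cannot be recovered.

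**4. Upper bound on the loss.** Detectable difference in SD units = (1.960 + 0.842) × √(1/n₁ + 1/n₂).
- 42/42: 0.611
- 39/39 or 40/38: about 0.634–0.635
- 41/37: 0.635

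Power for an assumed difference of 0.5 SD falls from 63.0% (42/42) to 59.8% (39/39).

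**5. What can be recovered.** With outcome variance σ², a carrier with both scans has residual variance σ²(1 − r²) after baseline adjustment. One with a follow-up scan only has variance σ², and so carries a fraction (1 − r²) of a full carrier's information. The relative gain from keeping six such carriers beside 78 full ones is 6(1 − r²)/78:
- r = 0.6: 6 × 0.64/78 = 4.9%
- r = 0.7: 6 × 0.51/78 = 3.9%
- r = 0.8: 6 × 0.36/78 = 2.8%

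**6. A caution on the simpler method.** The gains in step 5 belong to a likelihood-based longitudinal model, or to ANCOVA that gives the six a weight of 1 − r². If the pooled mean is filled in and all carriers are weighted equally, the variance of the treatment difference is proportional to [78(1 − r²) + 6]/84², against (1 − r²)/78 when the six are left out. The first is smaller only if 1 − r² > 468/(84² − 78²) = 468/972 = 0.481, that is r < 0.72. In terms of information:
- r = 0.6: gain of 3.5%
- r = 0.7: gain of 0.8%
- r = 0.8: loss of 4.4%

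The weights therefore matter.

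**The case against.** **The wording may be narrower than it looks.** The sentence on the other endpoints follows the LGE result and may mean that only LGE is affected. Nothing says outright that a readable follow-up scan will be discarded. This stands as a limit: removal from all five CMR components is an inference. But the image-quality sentence speaks of analyses in general, so the wider reading is the natural one, and the narrower one would need saying.

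**A missing baseline is a missing-data problem, not a departure from assigned groups.** This is largely right. The scan belongs to the first visit, so its quality is unlikely to depend on treatment, although the article does not state its timing relative to randomisation. Leaving the six out costs precision; the documents do not show bias.

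**The amended analysis plan may already deal with it.** A repeated-measures model can keep carriers without a baseline, and the choice of model is usually left to the analysis plan. That is fair for the model. It does not remove the mismatch between two statements that the article itself makes.

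**Stronger readings that the documents do not support.**
- A reader might infer that eligibility of the six cannot be confirmed, or that the population description is wrong. A local reading, or cine images good enough for LVEF but not for full core-lab analysis, could have established LVEF. The article simply does not show which applied.
- A reader might infer that the RV exclusion ("Global or regional RV dysfunction and/or structural alterations") also rested on MRI. Table 1 ties only LVEF to that modality, and Table 2 lists an echocardiogram at the first visit.
- A reader might take "all eligible carriers who have been randomised" as making the six ineligible for analysis. That sentence goes on to treatment-arm allocation and dosing, and says nothing about CMR quality.

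**Conclusion.** The point holds in a limited form. The handling rule for the six most naturally excludes them from the continuous CMR comparisons. That sits badly with the intention-to-treat statement, and the last-observation rule cannot repair it. At most 7.1% of the cohort is lost from five of the eight components, and the detectable difference rises from 0.611 to about 0.635 SD if the six would otherwise have been complete. A suitable model recovers about 3–5% in information, given r of 0.6–0.8 and six readable follow-up scans. Neither assumption can be checked in the article. For late enhancement the figure is only indicative, since 78 − 14 = 64 of the analysable carriers had none at baseline and the measure will be far from normal.

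The effect is modest, but the remedy is cheap and the trial is short of data. How LVEF was established for the six, and what denominators Table 4 uses, are reporting clarifications and no more.

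**What to change.** 1. State that each continuous CMR component is analysed, by assigned group, in all randomised carriers with a readable end-of-study scan, whether or not the baseline scan was adequate. Say which CMR components the six lack at baseline.
2. Use a constrained longitudinal model, with baseline and follow-up both as outcomes and a baseline mean common to the two arms. Alternatively, use ANCOVA with the missing baseline set to the pooled mean of both arms, with those carriers down-weighted by 1 − r² estimated from the complete carriers. State that the last-observation rule does not apply to a missing baseline.
3. For reporting, give per-arm denominators for every CMR row of Table 4, and add a sentence on the reading by which LVEF above 45% was established for the six.

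The cost is a change of wording in the analysis plan and some extra modelling, with no new data. The constrained model assumes equal baseline means in the two arms, which randomisation justifies.
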